## Abstract

**Background:**

Aquatic exercise is recommended by the Osteoarthritis Research Society (OARSI), by the American College of Rheumatology (ACR) and by the European League Against Rheumatism (EULAR) as a nonpharmacological method of controlling the knee osteoarthritis (KOA) symptoms. Moreover, given that weight loss results in a reduction of the load that is exerted upon the knee during daily activities, obesity is also considered to be a modifiable risk factor for the development and or exacerbation of KOA. The implementation of an exercise based weight loss program may, however, itself be limited by the symptoms of KOA. The aquatic program against osteoarthritis (termed “PICO” in Portuguese) prioritizes the control of symptoms and the recovery of functionality, with an attendant increase in the patient’s physical activity level and, consequently, metabolic rate. Our laboratory is assessing the effectiveness of 3 months of PICO on the symptoms of KOA, on physical function, on quality of life and on gait. In addition, PICO shall examine the effects of said exercise intervention on inflammatory biomarkers, psychological health, life style and body composition.

**Methods/Design:**

The trial is a prospective, single-blinded, randomized controlled trial, and involves 50 overweight and obese adults (BMI = 28–43.5 kg/m^2^; age 40–65 yrs) with radiographic KOA. The participants are randomly allocated into either an educational attention (control) group or an aquatic (exercise program) group. This paper describes the experimental protocol that is used in the PICO project.

**Discussion:**

The PICO program shall provide insight into the effectiveness of an aquatic exercise program in the control of KOA symptoms and in the improvement of the quality of life. As such, they are likely to prove a useful reference to health professionals who intend to implement any kind of therapeutic intervention based around aquatic exercise.

**Trial registration:**

NCT01832545.

## Background

Although rheumatic diseases (RD) have low death rates, they are one of the primary causes of compromised quality of life and absenteeism from work, with attendant economic and social consequences [1]. In Portugal, RD are responsible for 40 to 60% of situations of prolonged physical incapacity in daily activities, for 43% of cases of absenteeism from work, and for 35 to 41% of early retirements due to illness [2].

Osteoarthritis (OA) is the most prevalent rheumatic disease and represents a great risk to the quality of life of the individual, given the consequent loss of autonomy that can be precipitated by its effect on lower extremity based activities (such as walking up and down stairs, climbing and squatting) [1,3,4]. Although the causes of OA are not completely understood, it is thought to be a complex, adaptive response of the joints to biomechanical, genetic and environmental stresses [5]. Recent studies demonstrated that that low-grade inflammation plays a pathophysiological role in OA. The severity, the symptoms, the impairment in physical function and the progression of OA may also be partly mediated by the extent of chronic inflammation in OA patients [6,7].

The knee is the most commonly affected weight bearing joint, being considered the 4^th^ and 8^th^ main cause of disability in women and men, respectively [8]. KOA is more common in the medial tibiofemoral compartment than in other sites of the knee, probably due to a higher frequency of varus malalignment [9]. Inflammation and joint loading are commonly believed to cause or to exacerbate the disease process [10]. Obesity, prior knee injury, physical activity levels, physical strength and the extent of alignment/misalignment of body segments are the most often cited potential risk factors for KOA in the academic literature. The latter risk factor seems to have more importance in the radiographic progression than in the incidence of KOA [11-14].

Knee Osteoarthritis (KOA) is highly prevalent in obese individuals [15]. The International Association for the study of Obesity (IASO)/International Obesity Taskforce (IOTF) analysis (2010) estimated that approximately 1.0 billion adults are currently overweight and a further 475 million are obese, worldwide [16]. Obese individuals have higher concentrations of the inflammatory markers (such as TNF-α and leptin) that are predominantly secreted by adipose tissue and can induce the production of IL-6 and C-reactive protein (CRP) [17]. The pathogenesis of obesity is characterized by hypothalamic inflammation and subsequent central resistance to leptin. High leptin concentrations then compromise the reduction of food intake and increase in energy expenditure. In addition, leptin increases the synthesis of a stimulator of osteophyte formation, TNF-β [18]. The resulting low- grade inflammation plays a pathophysiological role in OA, because it can affect muscle function and lower the individual’s pain threshold. It can also affect chondrocyte homeostasis and cause degenerative changes in cartilage [6,10,19].

Besides its effect on the individual’s quality of life, KOA uses up considerable health care resources. The consequences of KOA make it a public health problem in many countries [1,20-22]. Pain is the symptom that markedly affects quality of life in KOA patients. Gait tests are an important measure of mobility and KOA patients may adapt their gait and adjust body alignment to reduce pain. However, the latter adaptations may increase the loading on the joint and result in increased disease progression. In addition, the pain that is concomitant with KOA causes irritability, sleeplessness, depression and other physical and psychological changes that may aggravate the disease and incur both a general loss of functionality and a drop or maintenance in physical activity levels to below the recommended levels [23]. The main consequences of inactivity are weight gain and the obesity installation [24]. The combination of obesity and KOA create a vicious cycle of pain, loss of functionality, and disease progression. To interrupt this cycle, KOA symptoms should be reduced. Physical activity and weight loss can make an important contribution.

Current therapy most often focuses on pain relief, using mainly analgesics and nonsteroidal anti-inflammatory medications that have only a modest functional benefit and do not slow disease progression, whilst causing serious cardiovascular and gastrointestinal side effects [25,26]. The recommendations of the Osteoarthritis Research Society International (OARSI), the American College of Rheumatology (ACR), and the European League Against Rheumatism (EULAR) also include exercise as an important treatment [27-29]. Aerobic, aquatic, and resistance training exercise are recommended [27].

### Exercise program and Knee OA

Appropriate exercise can provide an improvement in symptoms and reduce pain, preventing OA-associated disabilities and increasing quality of life. In addition, there seems to be a positive effect of exercise on the chondroprotective anti-inflammatory cytokine response [30], mediated by IL-10 and IL-4. The weight loss and body composition improvements that can induced by exercise, reduce the thigh fat depots and may have a positive effect on the secretion of pro-inflammatory cytokines, lowering IL-1 and leptin levels in individuals with KOA [10].

The literature indicates that an exercise intervention for KOA should be broadly based and include aerobic training, lower limb-strengthening, gait training, flexibility, stability and posture training, weight reduction, patient education and psychosocial intervention [27,31-34].

Aquatic exercise is at this moment one of the main non pharmacological interventions that is suggested by the OARSI, ACR and EULAR guidelines as a means of controlling the symptoms and to prevent or slow down the progression of KOA [26,27,35]. Various studies have demonstrated that controlled aquatic exercise classes can be effective for KOA symptom control and to improve function [36-43]. In addition, a person in pain has difficulty with weight bearing exercise. Aquatic exercise allows aerobic exercise to be accomplished with less load on the joints [44].

Several studies have examined the effects of exercise in water (hydrotherapy, aquatic exercise) on the symptoms of knee arthritis [36-40,44-51]. However, said studies are inconsistent as regards the quality and quantity of exercise that was performed. There is a lack of definition of what is involved in hydrotherapy and what is performed in aquatic exercise classes. Aquatic Exercise (AE) is an exercise modality which can be defined as a group of exercises performed in the water, mainly in the vertical position, with or without music, with or without equipment added and in shallow or deep water. Its main characteristics are the utilisation of hydrostatic pressure and hydrodynamics to work on the aerobic and neuromuscular system. AE has been used for rehabilitation (hydrotherapy) [52-59], for athletic training [60-64] or for general fitness activity [65-71].

Aerobic training is very important for pain control and to improve functionality in individuals with KOA [27]. According to the guidelines of the Aquatic Exercise Association (AEA) [72], aerobic aquatic exercise classes with fitness goals, should be performed in water between 28-30°C so as not to compromising the endocrine responses. Water temperatures above 32°C are recommended for passive work, relaxation techniques or for individuals with low movement levels, but are not advisable temperature for aerobic or strength based exercise [64]. In cases of patients with low aquatic abilities, the Arthritis Foundation Guidelines suggest a superior limit range of water temperature of 31°C [73].

The PICO program is an overall body fitness and mind based intervention through aquatic exercise involving an educational component that has been specifically created for individuals with KOA. Two recent studies regarding the aquatic exercise in KOA should be referred to [38,39], as they have a controlled methodology and were performed according to the AEA guidelines [72].

#### *Study aim*

To design an aquatic exercise program specific to knee osteoarthritis, with the goal of management of OA symptoms and the improvement of physical fitness. The PICO program is based around the first step for weight loss interventions in individuals with KOA being the control of pain and other symptoms. When KOA symptoms are controlled, patients learn that it is possible to live with the disease which in turn motivates lifestyle changes. The increase of physical activity due to lifestyle changes may then cause improvement in body composition. In this way 6 hypotheses are formulated: H1. 3 months of aquatic exercise will improve KOA symptoms (pain and stiffness) and physical function in obese individuals with KOA; H2. The gait parameters (gait speed, gait cycle, ground reaction forces and knee forces moments) of obese individuals with KOA can be improved by aquatic exercise; H3. Beyond fitness component and the exercises skills, aquatic exercise group classes can work as an educational component and to promote lifestyle changes. H4: The aquatic exercise program can improve mental status and quality of life. H5: The aquatic exercise program can cause a weight reduction or body composition change. H6: 3 months of aquatic exercise can have a positive effect on selected inflammatory biomarkers of KOA.

## Design/Methods

### Study design

PICO is a single-blinded, randomized controlled trial with 3 months duration. Participants will be randomly assigned to one of two groups: aquatic exercise (AE) and control group (CG). Figure 1 provides a flowchart of PICO design. Researchers and personnel responsible for data collection will be blinded four the group classes. The study protocol was approved by the Ethical Committee of the Faculty of Human Kinetics, Technical University of Lisbon. All participants will be informed about the procedures and potential risks and an informed consent will be obtained from them.

**Figure 1 F1:**
[figure not shown]
PICO flowchart.

#### *Sample*

Considering the calculation of the sample size, the studies of Messier (2009) [74] and Wang (2007) [44] were used as a reference, because they had a sample with similar characteristics and studied similar outcomes. Both showed that a reduction of symptoms in patients with OA of the knee led to a significant improvement (α < 0.05) of the primary outcome measure of self-reported physical function. To find an analogous improvement of self-reported physical function of approximately 25% between the baseline and final measurements in patients with KOA, the minimum number of patients that are required is 20 for the main outcomes. The latter number is based on a power (1-B) of 0.80 and a significance level of 5% (two-sided). When a dropout rate of 20% is taken into account, at least 25 participants must be involved at study onset.

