#### *Inclusion criteria*

The study sample will consist of 56 community-dwelling adults from the Lisbon area with: (1) age between 40 and 65 years; (2) 28.0 ≤ BMI ≤ 45 kg/m^2^; (3) unilateral or bilateral KOA diagnosed by knee pain and grade I-III radiographic tibiofemoral OA or tibiofemoral plus patellofemoral OA (4) a sedentary lifestyle, defined as not participating in a program that incorporates more than 30 minutes per week of formal exercise, within the 6 months leading up to the study; (5) being independently mobile; and (6) literate.

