### Statistical analysis

Descriptive statistics, including frequencies for categorical variables and means with standard deviations (SD) for continuous variables with normal distribution and median for skewed distributions will be used to describe subject’s characteristics. Normality will be tested using the Kolmogorov-Smirnov test. For continuous outcome measures, differences in mean change (baseline minus post-intervention) will be compared between groups using analysis of covariance adjusted for baseline values of the outcome. Comparisons between groups (CG and AEG) at baseline and post intervention will be conducted by Independent-sample t-tests or Mann–Whitney U test if equal variance is not assumed. Changes within group will be analyzed by paired Student’s t tests or by the Wilcoxon Signed Rank test when normality is not assumed. A mixed model analyses of covariance (ANCOVAs) will be conducted for interaction analyses adjusted for BMI with two within-participant factors of 6MWT (baseline) and 6MWT (post-intervention) and between two groups (CG and AE). Statistical analysis will be performed using IBM SPSS Statistics 20.0 and MedCalc Statistical Software (MedCalc Software, Mariakerke, Belgium). Multiple Linear regression analyses will be performed to understand the potential covariates that could improve the explanation of the variability of outcomes (6MWT, strength and KOOS dimensions). Statistical significance will be set at P *<* 0.05 (2- tailed) for all analyses. Effect sizes will be calculated for all measures with an effect size of 0.2 considered small, 0.5 medium and 0.8 large.

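### The sample size rests on a within-patient 25% change, so 80% power for the between-arm comparison is not established; the unit of 20 and 25 is unstated, and the total is 50 in one place and 56 in another

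*Protocol article*

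**What the plan says.** The Sample section of the protocol article takes two earlier studies as its reference and aims at an improvement in self-reported "function of approximately 25% between the baseline and final measurements in patients with KOA, the minimum number of patients that are required is 20". The 20 is described as "based on a power (1-B) of 0.80 and a significance level of 5% (two-sided"). After allowing for 20% dropout, "at least 25 participants must be involved at study onset". Neither 20 nor 25 is described as per arm or as a total. The section states no SD, no expected change in controls and no test.

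The Study design section describes two randomised groups, aquatic exercise and control. Under Statistical analysis, changes in continuous outcomes are "compared between groups using analysis of covariance adjusted for baseline values of the outcome". Within-group paired tests are also planned. The control arm attends twelve weekly 90-minute sessions of a weight-management education programme (Educational program: control group).

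On the planned size, the abstract says the trial "involves 50 overweight and obese adults". The Inclusion criteria say "The study sample will consist of 56 community-dwelling adults".

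**The concern.** The quantity that was powered and the quantity that will be tested are different. A baseline-to-final improvement in patients contains everything that moves the score over three months: the aquatic programme, regression to the mean, continued analgesic use, and attention. The randomised contrast removes whatever part of this the control arm shares. It also carries the sampling error of two means instead of one. A sample that is large enough for the first quantity need not be large enough for the second.

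Zero change in controls is not a safe default. They receive a structured weight-management programme, and the Background itself names weight loss as a contributor to symptom reduction.

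What is at stake is how the result will be read. The Conclusions expect the findings to support evidence-based recommendations. A non-significant between-arm result would be judged against an 80% power claim that the text does not support. A reader also cannot tell which enrolment figure the trial is to be held to.

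**Working it through.** **Inputs from the article.** Effect 25% (baseline to final); n = 20; power 0.80; two-sided alpha 0.05; dropout 20%; totals 50 and 56. **Not given, so assumed below.** SD, control-arm change, baseline-to-final correlation r, and allocation ratio (1:1 taken). Powers use the noncentral t distribution.

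**1. The plan's own figures.** The dropout step reproduces: 20 / (1 − 0.20) = 25. The 20 itself cannot be reproduced without an SD.

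**2. Unit and total.**
- 2 × 25 = 50, and (2 × 20) / 0.80 = 50. So 25 read as per arm agrees with the abstract.
- 56 / 2 = 28 per arm. After 20% dropout, 28 × 0.80 = 22.4, or about 22 completers per arm. This satisfies a minimum of 25 per arm but is a different planned total from 50.

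**3. Reading A: the 20 came from a paired test.** The paired t test has noncentrality d√n. With n = 20, power is 0.80 at d = 0.66 SD of change, so the implied SD of change is 25 / 0.66 ≈ 37.9% of the baseline mean.

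Now carry d = 0.66 to a two-sample t test, with noncentrality d√(n/2), n per arm and controls unchanged:

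| Completers per arm | Power, change scores |
|---|---|
| 10 (if 20 is the trial total) | 0.29 |
| 20 | 0.53 |
| 22 | 0.57 |

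The planned ANCOVA does better. Its residual variance is (1 + r)/2 times the change-score variance, so the effect in SD units becomes 0.66 / √((1 + r)/2). With 20 per arm:
- r = 0.5: 0.66 / 0.866 = 0.76, power 0.65.
- r = 0.7: 0.66 / 0.922 = 0.72, power 0.60.

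For 80% power at d = 0.66 with unchanged controls, change scores need 37 completers per arm. ANCOVA needs 28 (r = 0.5) to 32 (r = 0.7).

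If controls improve, the contrast shrinks. For illustration, with 20 per arm on change scores:
- controls improve 5%: difference 20%, d = 20 / 37.9 = 0.53, power 0.37;
- controls improve 10%: difference 15%, d = 15 / 37.9 = 0.40, power 0.23.

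**4. Reading B: the 20 is a per-arm two-sample figure.** With 20 per arm, 80% power needs d = 0.91. For a 25% difference between arms the SD must then be 25 / 0.91 ≈ 27.5%, and controls must not change. If both hold, the 80% claim is correct.

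**5. Detectable difference at the planned size.** For 80% power the between-arm difference must be about 0.91 SD with 20 completers per arm, or about 0.86 SD with 22. Under the planned ANCOVA, SD here means the residual SD. In change-score SD, the 0.91 becomes 0.91 × 0.866 ≈ 0.79 (r = 0.5) or 0.91 × 0.922 ≈ 0.84 (r = 0.7).

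**The case against.** The strongest reply is that the Sample section names no test. Reading B fits its wording if the 25% is taken as the aquatic arm's change against an inert control, and then the 80% stands. The SD may sit in the reference studies or in a fuller protocol. This part of the reply holds: a reader might infer that the 80% is wrong, or that the trial has only 53% power, and the article proves neither. Every power-loss figure above depends on Reading A. The control improvements and the values of r are assumptions; with r = 0.3, for example, ANCOVA power at 20 per arm would be 0.71.

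A reader might also infer three competing totals: 25, 50 and 56. The article does not support that. The 25 is a minimum without a unit, and two arms of 25 give the abstract's 50. The firm contradiction is 50 against 56.

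It can also be said that within-group tests are planned and that the Discussion calls the sample deliberately small. Neither answers the point. Within-group tests do not use the randomisation, and a small trial still needs a power statement for the comparison it makes. Reading B, for its part, needs an unchanged control arm and a 0.91 SD effect, and the article states neither.

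**Conclusion.** The point holds in this form. The sample size paragraph attaches 80% power to a within-patient change and supplies nothing that carries that power over to the randomised contrast, so the power of the between-arm ANCOVA is not established. No arithmetic error is shown.

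The size depends on how the 20 was derived. Under a paired derivation with unchanged controls, power at 20 completers per arm is about 53% on change scores, or about 60–65% with ANCOVA (r from 0.7 to 0.5), and lower if controls improve. Under a per-arm two-sample derivation it is 80%, but only for a difference of about 0.91 SD and unchanged controls. Equal SDs and 1:1 allocation are assumed throughout.

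Two defects do not depend on any assumption: the unit of 20 and 25 is missing, and the planned total is 50 in the abstract but 56 in the inclusion criteria.

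**What to change.** Rewrite the Sample paragraph as a between-arm statement for the planned analysis. If 50 is the total, for example:

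> Twenty-five participants will be randomised per arm (50 in total). With 20% dropout, 20 completers per arm give 80% power at two-sided 5% to detect a between-arm difference of about 0.91 residual SD in baseline-adjusted self-reported physical function.

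If 56 is the total, the figures become 28 randomised and about 22 completers per arm, with a detectable difference of about 0.86 residual SD. State that SD means the residual SD after baseline adjustment, and translate the difference into scale points with an SD that the authors can cite. If 20 and 25 were not meant per arm, say what they were.

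Drop the claim of 80% power for a 25% baseline-to-final change. Use one planned total in the abstract, the Sample section and the Inclusion criteria.

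The cost is rewording only: no extra patients and no change to the analysis. The price is a stated detectable effect that looks less favourable than the present text.

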#### *Inclusion criteria*

The study sample will consist of 56 community-dwelling adults from the Lisbon area with: (1) age between 40 and 65 years; (2) 28.0 ≤ BMI ≤ 45 kg/m^2^; (3) unilateral or bilateral KOA diagnosed by knee pain and grade I-III radiographic tibiofemoral OA or tibiofemoral plus patellofemoral OA (4) a sedentary lifestyle, defined as not participating in a program that incorporates more than 30 minutes per week of formal exercise, within the 6 months leading up to the study; (5) being independently mobile; and (6) literate.

#### *Exclusion criteria*

The exclusion criteria are: subjects with skin diseases, with unstable medical conditions and or who have undergone hip or knee replacement, or knee surgery within the 6 months prior to the study; and participants who had any type of knee injections within the past 3 months.

